### Outcomes {12}

The primary outcome of this study is to assess the impact of training general practitioners in motivational interviewing on the organized screening rate for CRC (CRC OS) at 24 months. The 24-month period varies and starts when individual patients are recruited.

The secondary outcomes are:
Assessing the impact of training general practitioners in motivational interviewing, on the organized screening rate for CRC (CRC OS) at 12 monthsExploring the ambivalence of patients with respect to the CRC OS by means of a self-questionnaire measuring the variables influencing health behaviors (health belief model) [28, 29] and exploring the opinion of patients on their life expectancy [30]. This assessment will take place at the start of the study, at 6 months, 12 months, and 24 months. It will be performed by all patients who have agreed to participate in the study.Exploring the reasons for patients who refused to take the test after 2 years.Identifying any difference in screening that could be linked to the patient’s gender, and quantifying this difference.

### Participant timeline {13}

The participant timeline is shown in Fig. 1.

**Fig. 1 Fig1:**
[figure not shown]
Enrolment, interventions, and assessments

### Sample size {14}

A classic randomized trial would require 752 subjects in total, for a power of 80%; an increase in the participation rate of 35 to 45%, and an alpha risk = 5% (two-tailed test). However, this power is here reduced by the existence of an intra-class correlation, measuring the degree of resemblance of the responses of patients from the same physician, quantified by the intra-class correlation coefficient ρ. The inflation factor by which to multiply the number of subjects is then (1+(m1) ρ), where m is the size of a cluster. The intra-class correlation coefficient (ICC) is typically of the order of 0.001 to 0.05. In the case of this study (CRC OS), an ICC value of 0.01 seemed reasonable. The correlation between doctors and patients is less important for screening procedures and the monitoring of acute pathologies than it is for the monitoring of chronic pathologies. With 82 GPs including patients and an average cluster size of 10 assessed patients per GP, the chosen coefficient is 1.09. A total staff of 820 patients divided between 82 doctors, will guarantee a power of 80%. With 5% lost to follow-up, the number of patients needed is 864 patients, which will be rounded up to 902, or 11 patients per GP to compensate for loss.

The software used for the statistical analysis will be R and SAS software, depending on the analysis.

### Recruitment {15}

A total of 902 patients will have to be recruited, or 451 patients per arm. In each arm, 41 GPs will need to recruit an average of 11 patients over a period of 1 year. This represents 1 to 2 recruitments per month per GP.

In Finistere, the medical density of GPs is 113 doctors per 100,000 inhabitants, or 885 patients per GP (STATISS 2015, ARS Bretagne), which ensures the feasibility of the study.

General practitioners recruit during their usual consultations. When a patient meets the eligibility criteria to join the study, the GP presents the study to him and suggests that they enter the protocol.

Recruitment is facilitated by patients who receive the CRC OS screening introductory letter usually sent during the national CRC OS promotion campaign, and who may mention it to their GP.

## Assignment of interventions: Allocation

### Sequence generation {16a}

GPs in the control and intervention group will be randomized. GPs who have received training in motivational interviewing in the past will be excluded. The stratification will make it possible to obtain 2 homogeneous groups of physicians in terms of the participation rate of their patients in screening the year preceding the study. This randomization will be carried out using groups of screening test prescribers defined by the Association for cancer screening in Finistere (CRCDC). GPs are divided into three screening profiles. Low screeners were defined as 0 to 19 screenings per year. Moderate screeners were defined as 20 to 100 screenings per year. High screeners were defined as more than 100 screenings per year For each doctor successively included in the trial, the randomization list will give his or her status as participating or not participating in the MI training. The allocation ratio is 1.

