### Trial design {8}

This study is a cluster randomized control trial with GPs practice as a cluster unit. The allocation ratio is 1. It is a superiority trial. GPs agreeing to participate are randomized into control or intervention groups according to their CRC screening profile. GPs are divided in three screening profiles. Low screeners were defined as 0 to 19 screenings per year. Moderate screeners were defined as 20 to 100 screenings per year. High screeners were defined as more than 100 screenings per year.

The control group is composed of GPs who have never participated in motivational interviewing training. They include their patients for the study, without changing their practice with respect to CRC OS.

The intervention group also consists of GPs, similar to those in the control group, who never participated in motivational interviewing training.

In a health center with more than one GP, there could be GPs who benefited from motivational training and GPs who haven’t. This could result in cross-contamination. The authors think this will be limited because the GPs who have motivational training are asked not to talk about motivational interviewing to the other GPs during the study and because motivational interviewing requires some practice, which the GPs in the control group will not have at all. The intervention is not about learning what motivational interviewing is but about practicing and mastering it.

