### Concealment mechanism {16b}

The allocation sequence is performed by opaque sealed envelopes, randomized in 1:1, stratified on the screening profile.

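### The GP strata are annual test counts that mix participation rate with list size, so they do not by themselves make the arms homogeneous in participation rate (minor)

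*Protocol article*

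**What the plan says.** Sequence generation {16a} states the purpose of stratifying the GPs: "The stratification will make it possible to obtain 2 homogeneous groups of physicians in terms of the participation rate of their patients in screening", with the year before the study as reference. The groups come from the regional screening centre (CRCDC), and the same section defines them: "Low screeners were defined as 0 to 19 screenings per year. Moderate screeners were defined as 20 to 100 screenings per year". Trial design {8} repeats the definitions and adds "High screeners were defined as more than 100 screenings per year". Concealment mechanism {16b} confirms that allocation is "randomized in 1:1, stratified on the screening profile" and names no other factor.

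Elsewhere the article treats participation as a proportion. Explanation for the choice of comparators {6b} gives a current rate of 35% in Finistère, and Sample size {14} is built on a rise from 35% to 45%. Recruitment {15} gives the one list-size figure: "113 doctors per 100,000 inhabitants, or 885 patients per GP".

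**The concern.** The stated property concerns a rate, but the stratifying variable is a count. A GP's yearly count is the participation rate multiplied by the number of listed patients due for a test. A large list with poor uptake and a small list with good uptake can therefore fall in the same band, or even in reversed order. Nothing in the definitions divides by an eligible population.

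A reader who relies on {16a} would regard the arms as already matched on the GP-level baseline closest to the primary outcome. If they are only loosely matched, some between-GP variation in prior uptake stays open to chance imbalance. A cheap covariate that could absorb it might then never be collected, because it seems unnecessary.

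**Working it through.** **1. The plan's own figures.** Per arm, n = [1.960·√(2·0.40·0.60) + 0.842·√(0.35·0.65 + 0.45·0.55)]² / 0.10² = 375.6, so 376, and 752 in total. The design effect is 1 + 9·0.01 = 1.09, and 752·1.09 = 819.7, so 820. Then 820/0.95 gives 864, and 82·11 = 902. Also 100,000/113 = 885. All agree with Sample size {14} and Recruitment {15}, and none is in dispute.

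**2. Cut-points expressed as rates.** Inputs from the article: mean list 885 and a test every 2 years (Background and rationale {6a}). Assumptions: share of the list aged 50-74 is 30% (range 25-35%), and half of these are due each year. Due per year = 885 · share / 2; rate = count / due.

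| Share 50-74 | Due per year | Tests at 35% uptake | Rate at 20 tests | Rate at 100 tests |
|---|---|---|---|---|
| 25% | 111 | 39 | 18% | 90% |
| 30% | 133 | 46 | 15% | 75% |
| 35% | 155 | 54 | 13% | 65% |

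An average-list GP is thus moderate over most plausible rates. In reverse, at a 30% share, a GP at exactly 35% is low only with a list under 20/(0.15·0.35) = 381 and high only above 100/(0.15·0.35) = 1,905.

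**3. How well the count tracks the rate.** The article gives no spread of list sizes or of GP rates, so both are assumed. The simulation uses beta-distributed GP rates with mean 35%, lognormal lists with mean 885, and a 30% share. Between-GP SD = √(ICC·0.35·0.65), which is 4.8 points at ICC 0.01 and 10.7 points at 0.05.

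| ICC | CV of list size | Correlation of count with rate | Correlation of count with list | Variance in rate explained by strata | GPs in moderate | Mean rate low / moderate / high |
|---|---|---|---|---|---|---|
| 0.01 | 0.3 | 0.39 | 0.85 | 2% | 98% | 0.30 / 0.35 / 0.40 |
| 0.01 | 0.5 | 0.25 | 0.93 | 3% | 89% | 0.33 / 0.35 / 0.38 |
| 0.05 | 0.2 | 0.79 | 0.52 | 14% | 95% | 0.17 / 0.36 / 0.57 |
| 0.05 | 0.3 | 0.67 | 0.66 | 17% | 92% | 0.20 / 0.36 / 0.52 |
| 0.05 | 0.5 | 0.50 | 0.81 | 17% | 83% | 0.25 / 0.36 / 0.46 |

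The mean rate rises from low to high in every row, so the strata carry information on rate. They carry only part of it, and most GPs fall in one band.

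**4. Chance imbalance in mean GP rate, 41 versus 41 GPs.** Under simple randomisation the 95% range is ±1.96·SD·√(2/41): ±1.96·4.8·0.221 = ±2.1 points at ICC 0.01, and ±1.96·10.7·0.221 = ±4.6 points at ICC 0.05. For a given ICC these are upper limits, because the count strata remove some of the imbalance.

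**5. The most a covariate could gain.** Assessed patients: 902·0.95 = 857, or 10.45 per GP. Power for 35% versus 45% is 81.6% at ICC 0.01 (design effect 1.0945), 69.3% at ICC 0.05 (1.4725) and 84.9% with no between-GP variance. A covariate that explained all between-GP variation would therefore raise power from about 82% to 85% at ICC 0.01, and from about 69% to 85% at ICC 0.05.

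**The case against.** The strongest reply is that using the registry's existing prescriber groups is a legitimate, practical choice, and that little depends on it. Randomising 82 GPs is unbiased whatever the strata. The design effect in Sample size {14} already pays for between-GP variation, and Statistical methods {20a} plans a GEE with sandwich variance. At the protocol's ICC of 0.01 rates vary little, so there is little to balance; where they vary more, counts track them better. The 69% power comes from substituting ICC 0.05 and is not caused by the stratification. All of this stands, and it is why the point is minor. What it leaves untouched is that {16a} claims homogeneity in a quantity the strata do not measure.

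A reader might also infer more than the documents support:

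- *That the strata mainly sort GPs by list size.* In the simulation this is so at ICC 0.01 once the CV of list size exceeds about 0.14. At ICC 0.05 it is a tie at a CV of 0.3 and reversed at 0.2. The article reports a mean list only.
- *That there is no balance on rate at all.* Counts correlate positively with rate in every scenario run.
- *That the counts come mostly from repeat participants, while the trial enrols people who have never participated.* The eligibility restriction is real, but the article gives no split of first and repeat tests.

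Finally, covariates in the primary model are commonly left to the SAP, which is not shown. Their absence from {20a} is not counted as an error here.

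**Conclusion.** The point holds as a minor one: {16a} states a property that the stratification does not deliver. The strata balance test volume, which is an imperfect proxy for participation rate. The moderate band alone spans about 15-75% uptake for an average list (18-90% to 13-65% across the assumed age shares), so balance on rate is partial. How partial cannot be settled from the article.

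The residual chance imbalance in mean GP rate is at most about ±2.1 points at ICC 0.01 and ±4.6 points at ICC 0.05, against a 10-point target difference. These figures borrow the ICC that Sample size {14} sets for trial patients' responses; the ICC of whole-list uptake may differ. It would be wrong to conclude that the comparison is biased or the trial undersized: unbiasedness, sample size and type I error are all unaffected.

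**What to change.** 1. Correct Sequence generation {16a} to say that the strata balance annual test volume, an imperfect proxy for participation rate.
2. Obtain from the CRCDC, for each of the 82 GPs, the participation rate before randomisation (patients tested divided by patients eligible on the list), and report it by arm.
3. Before any comparison of outcomes by arm, including the 6- and 12-month interim analyses, pre-specify that rate and the screening-profile stratum as GP-level covariates in the primary GEE. If the SAP already does so, only items 1 and 2 remain.

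Redefining the strata is probably no longer possible. Intervention GPs include patients only after three training sessions spaced 3 months apart, and recruitment began in June 2021.

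The cost is one extra GP-level extraction and a sentence in the analysis plan, with no added patients or visits. The CRCDC runs the invitations and holds participation data, and Confidentiality {27} lists the attending physician among the fields accessed. The extraction therefore looks feasible, but the article does not show that eligible denominators per GP are held, so this should be confirmed. The gain is small at ICC 0.01 (at most about 82% to 85% power) and larger if the ICC is higher.

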### Concealment mechanism {16b}

The allocation sequence is performed by opaque sealed envelopes, randomized in 1:1, stratified on the screening profile.

### Implementation {16c}

The recruitment of GPs will be carried out by the authors. It will be done initially by mail, followed by 3 reminders every month by email or by phone. These GPs will be contacted from the list of the Finistère order of doctors. GPs who say they have already been trained in motivational interviewing are excluded. Randomization will be carried out by the data management unit of the CHRU of Brest.

## Assignment of interventions: Blinding

### Who will be blinded {17a}

As the study is based on the participation of GPs in training, the trial is necessarily open to physicians. However, patients will not know if their doctor has received training in motivational interviewing and will be assigned randomly in groups. The outcome assessment is objectively measured electronically.

### Procedure for unblinding if needed {17b}

Only outcome assessors and patients are blinded so unblinding will not occur.

## Data collection and management

### Plans to promote participant retention and complete follow-up {18b}

No compensation is provided for patients.

### Data management {19}

All the information required by the protocol will be recorded in an electronic case report form (CRF). The data will be disseminated as and when they are obtained, and explicitly recorded in these notebooks. Each missing item must be coded. The online filling of the observation notebook by the investigator allows the data to be viewed quickly and remotely. The investigator is responsible for the accuracy, quality, and relevance of all data entered. In addition, when entered, this data is immediately verified through consistency checks. As such, it will validate any change in value in the CRF. These modifications are subject to an audit trail. A justification can be included as a comment. A paper printout will be requested at the end of the study, authenticated (dated and signed) by the investigator. A copy of the authenticated document intended for the sponsor will be archived by the investigator.

Data entries will be carried out electronically via an internet browser. The setting of the CRF as well as the data management of the study data will be carried out by the data management unit (DMU) of the CHRU of Brest using the Ennov Clinical software®. The data analysis will be carried out by the statistical service of the DMU of the CHRU of Brest using SAS and R software. The CRCDC data extraction (i.e., has the screening been carried out or not) will be done on their business software, Lynx®, thanks to the IT services company in charge of the development of this tool. The data required for the study will be integrated into the clinical database using the CS Import module of the Ennov Clinical software.

### Confidentiality {27}

This study requires access to data from directly identifying medico-administrative databases (name, maiden name, first name, date of birth, welfare number, affiliation fund, attending physician, postal address, telephone, date of last update), the “reference methodology” (MR-OO1) in the application of the provisions of article 54 paragraph 5 of the law n°78-17 of January 6, 1978, as amended relating to data processing, files and to freedoms does not apply, and it is necessary to apply for authorization from the *Commission Nationale de l’Informatique et des libertés* (CNIL) in order to be able to access this identifying data. The data processing also complies with the General Data Protection Regulation of the European Union No. 2016/679.

In accordance with the provisions concerning the confidentiality of data to which the persons responsible for the quality control of research have access (Article L.1121-3 of the Public Health Code), in accordance with the provisions relating to the confidentiality of information, in particular related to the nature of the products, the tests, the people who are suitable for them and the results obtained (article R.5121-13 of the public health code), the people with direct access will take all the necessary precautions to ensure confidential information relating to the products, the test, the persons who are suitable for them and particularly regarding their identity and the obtained results. These people, as the investigators themselves, are subjected to professional secrecy (under the conditions defined by articles 226-13 and 226-14 of the penal code). During or at the end of the research, the data collected on suitable people and sent to the sponsor by the investigators (or any other specialized stakeholders) will be coded. They must not in any case show the names of the persons concerned or their addresses in clear. Only the first letter of the subject’s last name and first name will be recorded, along with a study-specific coded number indicating the order of inclusion of subjects. The sponsor will ensure that each person who is involved in the research has given their written consent for access to the individual data concerning them and is strictly necessary for the quality control of the research.

### Plans for collection, laboratory evaluation, and storage of biological specimens for genetic or molecular analysis in this trial/future use {33}

There will be no biological specimens collected.

## Statistical methods

### Statistical methods for primary and secondary outcomes {20a}

A descriptive analysis of GPs and recruited patients will be carried out using the usual statistical parameters: frequency and percentage for qualitative variables; number, mean, standard deviation, median, quartiles, minimum, and maximum for quantitative variables. The comparison of response rated between the two groups takes into account the within-class correlation indicated by cluster randomization. A GEE logistic model (Generalized Estimating Equations, Liang & Zeger, 1986) will be used, with the “sandwich” estimator of the variance matrix. The GEE method requires retaining the structure of the correlation matrix describing the similarity of response within the same cluster. For cluster randomized trials, it is natural to assume that this matrix is “swappable” in shape. This modeling can obtain an odds ratio with a confidence interval not biased by the existence of an intra-class correlation. The analysis of the secondary criteria used, for the same reasons, a mixed linear model making it possible to take into account the intra-class correlation using an “exchangeable” structural correlation matrix. It is an intention-to-treat analysis.

For people who have not completed their 24-month test, open individual telephone interviews will be conducted to explore the reasons.

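### GPs are randomised within three screening-profile strata, but the described primary GEE has no stratum term: a small cost at the planned ICC, larger if the ICC is underestimated

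*Protocol article*

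**What the plan says.** Trial design {8}, Sequence generation {16a} and Concealment mechanism {16b} agree that GPs are allocated "randomized in 1:1, stratified on the screening profile". There are three profiles, defined by annual test counts: 0 to 19, 20 to 100, and more than 100. The stated purpose is prognostic balance: "The stratification will make it possible to obtain 2 homogeneous groups of physicians in terms of the participation rate of their patients" in the year before the study.

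Statistical methods {20a} describes the primary analysis in some detail: a logistic GEE, sandwich variance, an exchangeable within-GP correlation, and an odds ratio with its confidence interval. The one design feature it brings into the comparison is clustering: "The comparison of response rated between the two groups takes into account the within-class correlation indicated by cluster randomization". Secondary criteria use a mixed linear model with the same correlation structure. The screening profile appears in neither description. Methods for additional analyses {20b} announces nothing further.

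Sample size {14} compares 35% with 45% at 80% power and two-sided 5%, then applies one design effect. It says that "an ICC value of 0.01 seemed reasonable", after giving 0.001 to 0.05 as the typical range. It takes no credit for stratification.

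**The concern.** Stratified allocation balances the arms on profile. If profile predicts uptake, differences between strata no longer contribute to chance differences between the arms. A model without the strata still counts those differences as between-GP noise. Its standard error then exceeds the true variability of the estimate, the interval is too wide, and the real type I error is below the nominal 5%.

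The protocol's own reason for stratifying is that profile relates to participation. Followed as written, the analysis would therefore not use the precision that the design was meant to provide. At stake is efficiency and calibration. The error is in the conservative direction, and the effect estimate is not biased.

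**Working it through.** **Inputs from Sample size {14}:** rates 35% and 45%; two-sided alpha 0.05; power 80%; 82 GPs; 10 assessed patients per GP; ICC 0.01 (typical range 0.001 to 0.05).

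**Input not in the documents:** f, the share of between-GP variance explained by the three strata. It is varied from 0 to 1.

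**Step 1, the plan's own figures.**
- The pooled two-proportion formula gives 376 per arm, 752 in total.
- Design effect: 1 + (10 − 1) × 0.01 = 1.09, and 752 × 1.09 = 819.7, so 820.
- With 5% loss: 820 / 0.95 = 863.2, so 864. Recruitment target: 82 × 11 = 902.
- Power at 820 is 80.1% by the same formula.

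All stated figures reproduce. The 80% is the power of a comparison that ignores strata.

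**Step 2, formulas** (unpooled variance, so the baseline power is 80.3%).
- V = (0.35 × 0.65 + 0.45 × 0.55) / 410 = 0.0011585.
- Variance that the unadjusted model estimates: V × DE_u, with DE_u = 1 + 9 × ICC.
- True variance with strata balanced by design: V × DE_s, with DE_s = DE_u − 10 × f × ICC.
- SE_u and SE_s are the square roots of these two variances.
- True alpha without strata: 2 × [1 − Φ(1.96 × SE_u / SE_s)].
- Power without strata: Φ((0.10 − 1.96 × SE_u) / SE_s).
- Power with strata: Φ(0.10 / SE_s − 1.96).

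**Step 3, worked case, ICC 0.01 and f = 1 (the upper bound).**
- DE_u = 1.09 and DE_s = 0.99, so SE_u = 0.03554 and SE_s = 0.03387, ratio 1.049.
- Alpha = 0.040.
- Power without strata = Φ((0.10 − 0.0697) / 0.03387) = 81.5%.
- Power with strata = Φ(2.952 − 1.96) = 84.0%.

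**Step 4, the range.**

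| ICC | f | SE ratio | True alpha without strata | Power without strata | Power with strata |
|---|---|---|---|---|---|
| 0.01 | 0 | 1.000 | 0.050 | 80.3% | 80.3% |
| 0.01 | 0.5 | 1.024 | 0.045 | 80.9% | 82.2% |
| 0.01 | 1 | 1.049 | 0.040 | 81.5% | 84.0% |
| 0.03 | 0 | 1.000 | 0.050 | 74.1% | 74.1% |
| 0.03 | 0.5 | 1.065 | 0.037 | 75.5% | 79.3% |
| 0.03 | 0.8 | 1.110 | 0.030 | 76.4% | 82.5% |
| 0.05 | 0 | 1.000 | 0.050 | 68.4% | 68.4% |
| 0.05 | 0.5 | 1.099 | 0.031 | 70.1% | 76.5% |
| 0.05 | 0.8 | 1.175 | 0.021 | 71.4% | 81.8% |

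At a given ICC, power without strata rises slightly with f, because the true variance falls while the estimated one does not. Leaving the strata out therefore forgoes a gain; it does not take power below that of the unstratified calculation.

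**Step 5, simulation check.** With 82 clusters of 10 and total ICC 0.01, power without strata was 80.9% to 82.0%. Type I error was 5.4% with no stratum effect and 4.4% when the strata carried all of the ICC. The 5.4% is the known slight optimism of an uncorrected sandwich variance with this many clusters.

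**The case against.** **The article is silent; it does not say that the model is unadjusted.** An analysis plan that is not shown may list the covariates. This stands as a caution: one cannot say that the trial will ignore the strata. But {20a} fixes the link, the variance estimator and the correlation structure, and names the design feature accounted for. The stratification factor belongs in that same description.

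**The profile may predict little.** Eligible patients have never taken part in organised screening, whereas a GP's annual volume can include repeat participants. The strata are also counts ("Low screeners were defined as 0 to 19 screenings per year") and so depend on list size, although the stated aim is balance on a rate. This stands too. It is why the size is shown over a range of f, and why nothing here treats profile as a known strong predictor.

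**A reader might infer that the stated 80% power is lost.** The documents do not support that: the 820 patients were sized for an unstratified comparison, and at ICC 0.01 power without strata is 80.3% to 81.5%. Larger losses can be produced by assuming wide stratum rates. Simulations with control rates of 25/35/45% and 20/35/50% gave 75% and 64% without strata. But those scenarios imply total ICCs of about 0.026 and 0.053, the second beyond the article's range, and a marginal difference somewhat below the planned 10 points. Most of that shortfall belongs to the ICC assumption. With no stratification at all, those ICCs give about 75% and 68%.

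**Conclusion.** The point holds as one of efficiency and calibration. The allocation is stratified on a factor chosen for its expected relation to participation, and the described primary model does not include it. If profile predicts uptake, the test is conservative; if it does not (f = 0), nothing is lost.

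At the planned ICC of 0.01 the cost is small: a standard error 0 to 4.9% too large, alpha between 0.040 and 0.050, and at most about 2.5 points of power forgone (84.0% against 81.5%). The stated 80% is still met. At ICCs of 0.03 to 0.05 with f between 0.5 and 0.8, power is about 70 to 76% without strata and about 77 to 83% with them. In that region the stratum term recovers much or all of the shortfall that an underestimated ICC would cause.

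These figures assume equal clusters of 10, 820 assessed patients, a 10-point marginal difference and exact stratum balance. The value of f is an assumption throughout. It would go beyond the documents to state as fact that the interval is too wide or that the planned power is lost.

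**What to change.** In {20a}, name the three-level screening profile used at randomisation as a fixed factor in the primary GEE and in the secondary mixed models. Settle this before any outcome data are seen, including those for the 6- and 12-month analyses, which Interim analyses {21b} places under the same rules.

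In a logistic model with strata, the arm coefficient is conditional on stratum. Report the marginal effect by standardising over the strata, so that it answers the planned 35% versus 45% comparison.

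The cost is a sentence of text and two parameters against 82 clusters; the profile is already known for every randomised GP. One caution: removing arm-by-stratum means with no degrees-of-freedom correction gave a simulated type I error of 6.1% to 6.4%. That used six fitted means, against four parameters in the proposed model, so it overstates the problem. Even so, the plan should say whether a small-sample correction to the sandwich variance will be applied.

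No further covariate is needed for this point. In particular, the documents do not show that a prior-year participation rate per GP, with an eligible-list denominator, is available.
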